#### Secondary study parameters

- Difference in change in PRUNE: Linear generalized estimating equation (GEE) analyses will be used to study the longitudinal relationship between treatment group (determinant) on the one hand, and BCTQ score (outcome variable) on the other hand. This will be done for the different domains of the PRUNE.- Difference in PREM vs change in PROM: The PREM score is a continuous outcome and will be analyzed using an independent T-test if distributed normally and a Mann–Whitney U test when not. The change in PROM (BCTQ) score is a continuous outcome and will be analyzed using a paired T- test if distributed normally and a Wilcoxon signed rank test when not. To assess the association between PREM scores and PROM change scores, linear regression analyses will be performed. Multivariable regression models will be used to adjust for potential confounding of various patient and disease characteristics, including age, sex, body mass index, smoking and duration of disease. All domains of the PREM (pre-, intra- and postoperative care and communication) were introduced simultaneously in the same model as independent to determine to what extent the variation in treatment outcome between patients could be explained by the experience with health care, as measured by the PREM. The outcome is measured by the beta-coefficient, showing the change in PROM associated with 1 absolute point increase in PREM subscale.- Sensibility: Sensibility is measured using two-point discrimination, resulting in a categorical outcome. The outcome includes > 2 categories and will be compared using a Chi-Squared test.- RTW, Complications, Scar Aesthetics: Return of full function in days, number of complications and scar aesthetics are continuous outcomes and will be analyzed using an independent T-test.- Correlation between VAS, Bishop, two-point discrimination and both PROMs: The association between VAS score, Bishop score, two-point discrimination and PROMs (both BCTQ and PRUNE) will be determined using the Pearson or Spearman correlation, depending on the data distribution. Analyses will be performed in two dimensions: 1) the correlation between preoperative VAS score, Bishop score, two-point discrimination and both PROMs and 2) the association between change in VAS score, Bishop score, two-point discrimination and both PROMs (12-month score minus preoperative score).

Difference in surgical characteristics: Characteristics of surgery includes continuous outcomes (operation time, length of the skin incision, length of decompression to distal in cm, length of decompression to proximal in cm and total length of decompression in cm) and a binary outcome (intraoperative nerve luxation). The continuous outcomes will be analyzed using an independent T-test and the binary outcome using Fisher exact testing.

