### Secondary objectives

- To compare the change in PRUNE between open and endoscopic cubital tunnel release compared to the score of the BCTQ;- To compare the PREM between open and endoscopic cubital tunnel release, and assess its association with PROM;- To compare the post-operative recovery of sensibility;- To compare the return to work/full function;- To compare the complications;- To compare the scar aesthetics;- To compare the correlation between Visual Analog Scale (VAS) score (0-10, 0 being no pain to 10 being the worst pain), Bishop score (a 5 point scale, resulting in a total score of poor 0-2, fair 3-4, good 5-7, excellent 8-9) [16], two-point discrimination and both PROMS (BCTQ and PRUNE).

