#### Secondary outcomes

- The difference in change (Δ, preoperatively and postoperatively) in PRUNE score between both treatment groups at 3, 6, 12 and 18 months follow-up;- The difference in PREM between both treatment groups at 3 months follow-up and its effect on the change (Δ, preoperatively and postoperatively) in PROM;- The difference in post-operative recovery of sensibility between both treatment groups at 3, 6 and 12 months follow-up;- The difference in time until return of full function (RTW) in days between both treatment groups;- The difference amount of complications between both treatment groups during the follow-up period of 18 months;- The difference in scar aesthetics between both treatment groups at 12 months follow-up;- The (difference in) correlation between VAS score (0-10, 0 being no pain to 10 being the worst pain), Bishop score (a 5 point scale, resulting in a total score of poor 0-2, fair 3-4, good 5-7, excellent 8-9) [16], two-point discrimination and both PROMs (BCTQ and PRUNE) at 3, 12 and 18 months follow-up;- The difference in surgical characteristics (duration of procedure, length of incision, amount of peroperative subluxation of the nerve after release) between both treatment groups.

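### The chi-squared test planned for sensibility ignores the order of the two-point discrimination categories and, as written, the pre-operative measurement; the cost is power and interpretability, not validity.

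*Protocol article*

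**What the plan says.** The Secondary objectives of the Protocol article include: "To compare the post-operative recovery of sensibility". The Secondary outcomes turn this into a between-arm outcome: "The difference in post-operative recovery of sensibility between both treatment groups at 3, 6 and 12 months follow-up". No pre-to-post difference is written into that line. The PRUNE line in the same list does have one: "The difference in change (Δ, preoperatively and postoperatively) in PRUNE score between both treatment groups at 3, 6, 12 and 18 months follow-up".

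The analysis is given under Secondary study parameters: "Sensibility is measured using two-point discrimination, resulting in a categorical outcome". It continues: "The outcome includes > 2 categories and will be compared using a Chi-Squared test". That is the whole of the stated comparison.

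Further down, the same section uses two-point discrimination in a correlation analysis. One part is "the correlation between preoperative VAS score, Bishop score, two-point discrimination and both PROMs". The other part uses change, defined as "12-month score minus preoperative score". The correlations "will be determined using the Pearson or Spearman correlation, depending on the data distribution".

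**The concern.** Two-point discrimination is a graded measure, so categories formed from it run from better to worse. A Pearson chi-squared test treats them as unordered labels. It spreads its sensitivity over every kind of difference between the arms, and its statistic carries neither a direction nor an effect size.

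The outcome is also called recovery, which implies a reference to the pre-operative state. That reference value is obtained, because the correlation analysis needs it, but it does not appear in the comparison between arms. Within one section the measure is handled as unordered for the group comparison and as ordered or numeric for the correlations.

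At stake is the usefulness of one secondary outcome. The Discussion paragraph of the Abstract intends objective outcomes to be combined with subjective ones to differentiate the techniques, and patients are not blinded. A non-significant result from a weak test could be misread as showing that sensory recovery is the same after both operations.

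**Working it through.** **Inputs from the article.** Evaluable patients: 160 × 0.90 = 144, which agrees with Sample size, recruitment and consent. Allocation is 1:1, so 144 / 2 = 72 per arm. Significance level 0.05, taken as two-sided. The article states no power for sensibility, so there is no figure to reproduce.

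**Assumed inputs, not in the article.** Control-arm category probabilities 0.5/0.3/0.2 (three categories) or 0.4/0.3/0.2/0.1 (four), and a proportional odds ratio of 2.0 or 2.5.

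**Step 1: order does not enter the statistic.** For the invented counts 10/20/42 against 20/20/32, X² = 4.68 and p = 0.096 in each of three column orders tried.

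**Step 2: one ordered example.** Take 12/28/32 against 22/28/22, with 72 per arm. Column totals are 34, 56 and 54, so expected counts per arm are 17, 28 and 27. Then X² = 2 × (5²/17) + 0 + 2 × (5²/27) = 2.94 + 1.85 = 4.79 on 2 df, p = 0.091. The Wilcoxon-Mann-Whitney test on the same counts gives p = 0.033.

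**Step 3: power under an ordered shift.** An odds ratio of 2.0 doubles each cumulative odds.
- Three categories: cumulative odds 1 and 4 become 2 and 8, giving probabilities 0.667/0.222/0.111.
- Four categories: 0.667, 2.333 and 9 become 1.333, 4.667 and 18, giving 0.571/0.252/0.124/0.053.

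The chi-squared non-centrality is λ = n Σ (p − q)²/(p + q), with n = 72 and p, q the category probabilities in the two arms.
- Three categories: λ = 72 × (0.0238 + 0.0116 + 0.0254) = 4.38 on 2 df, power about 45%.
- Four categories: λ = 72 × (0.0303 + 0.0042 + 0.0179 + 0.0147) = 4.83 on 3 df, power about 43%.

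Simulation agrees and adds the rank test:

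| Odds ratio | Categories | Chi-squared | Rank test |
|---|---|---|---|
| 2.0 | 3 | 44% | 55% |
| 2.0 | 4 | 42% | 60% |
| 2.5 | 3 | 68% | 78% |
| 2.5 | 4 | 66% | 82% |

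Type I error was near 5% for both tests.

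**Step 4: the pre-operative value.** A second simulation cut a normal latent scale into 3 to 5 categories, with a shift of 0.5 SD and a pre/post correlation of 0.3 to 0.7 (all assumed). Power was 58–67% for chi-squared on the post-operative categories, 74–80% for the rank test, and 76–95% for a rank analysis of covariance using the pre-operative category. Setting by setting, the adjustment added about 2 to 16 points. Subtracting the baseline did less well than adjusting for it: with three categories and correlation 0.3, a rank test of change had 54.5% power, against 73.9% for the unadjusted rank test and 76.1% for the adjusted analysis.

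**Step 5: when the effect is not a consistent shift.** Against 0.5/0.3/0.2, an arm with 0.6/0.3/0.1 gives 34% (chi-squared) and 32% (rank). An arm with 0.5/0.43/0.07 gives 61% and 11%.

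**The case against.** The strongest reply is that the planned test is valid. Patients are randomised 1:1, so comparing sensibility after surgery between arms is a fair treatment comparison, and chance imbalance at baseline costs precision only. This stands. A reader might infer that the analysis fails to measure recovery or is biased; neither follows. It compares status without reference to the pre-operative value, which is harder to interpret as recovery but is not wrong.

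Second, the article never says that the categories are purely post-operative. Categories of change, such as improved, unchanged or worse, would fit its wording. Post-operative status is the plain reading, supported by the missing pre-to-post difference in the outcome line, but it remains an inference. Under either reading the order is ignored.

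Third, a reader might infer that the trial could not tell which technique does better. The frequency tables promised in the Analysis plan would show direction; only the test itself supplies none.

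Fourth, it is tempting to call sensibility the main objective outcome, or to call the two uses of two-point discrimination incompatible. The article ranks it nowhere above the other secondary outcomes. Spearman correlation works with ordered codes, so the two uses are inconsistent in approach but each can be carried out.

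Fifth, the power figures rest on assumed distributions, and the main comparison is generated under the model that favours the ordinal test. Step 5 shows that the advantage can disappear or reverse. That also stands and limits the claim.

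Finally, category boundaries and coding may sit in a full protocol or analysis plan that is not shown, and their absence is not criticised. The choice of test is stated in the article, so it is open to review.

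**Conclusion.** The point holds as a matter of efficiency and interpretability for one secondary outcome. The stated test discards the order of the categories and gives no directional estimate. As written, it also leaves unused a pre-operative measurement that is collected and used elsewhere in the same section.

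Under an assumed proportional odds ratio of 2.0 with 72 per arm, ignoring order costs about 11 points of power with three categories (55 − 44) and about 18 with four (60 − 42). At an odds ratio of 2.5 the loss is about 10 and 16 points. These sizes depend on the assumed category distributions and on an effect that shifts patients in roughly the same way across all categories. The further gain from the pre-operative category depends on how strongly the pre- and post-operative values are correlated, which the article does not give. There is no evidence of an inflated error rate. The change is worth making, but it does not affect the primary BCTQ analysis.

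**What to change.** Replace the chi-squared test by an ordinal analysis, for example a proportional-odds model or an ordinal GEE over the visits at which sensibility is examined. Include treatment, visit and pre-operative category, and report the common odds ratio with its 95% confidence interval. If the raw distance is recorded, analyse that instead with the baseline value as covariate. Entering the baseline as a covariate ties the result to the pre-operative state without forming differences between categories.

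Only the analysis wording changes: the measurements are already planned, and GEE is already the method for the BCTQ and PRUNE. The price is that the proportional-odds assumption must be checked, and that power is lower than with chi-squared if the effect is confined to some categories. Keeping the category frequencies by arm in the report would let readers see such a pattern.

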#### Analysis plan

Descriptive statistics will be provided using mean with standard deviation (SD), median with interquartile range (IQR) or frequencies/percentages depending on the type of distribution of the data. Distribution of data will be assessed using histograms and skewing.

Values of *p* < 0.05 will considered statistically significant. All analysis will be on an intention- to-treat basis. We will correct for multiple testing, *P*-values will be corrected by the Bonferroni method [21].

For exclusion and dropout, numbers and reasons are reported to ensure internal validity. A flow- chart will show the number of patients lost during follow-up including reasons for the loss of follow-up. An analysis on basic characteristics will be performed to control for selection bias. Missing values will be imputed using multiple imputations when meeting the assumption of missing completely at random/missing at random (MCAR/MAR), as imputation will always increase precision and often also reduce bias [22, 23].

Table 1 shows the variables at each study visit.

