**Methods:**

A prospective single-center open randomized non-inferiority trial will take place at the Plastic Surgery Department in the Jeroen Bosch Hospital, the Netherlands. 160 patients with cubital tunnel syndrome will be included. Patients are allocated to endoscopic or open cubital tunnel release by randomization. The surgeon and patients are not blinded for treatment allocation. The follow-up time will take 18 months.

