### Objectives

We hypothesize that endoscopic cubital tunnel release is more effective in treating cubital tunnel syndrome than open cubital tunnel release in both primary and secondary outcomes.

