### Trial design

This is a prospective randomized non-inferiority trial with two parallel study groups to assess the efficacy, patient treatment experience and safety profile of the open or endoscopic release in patients with cubital tunnel syndrome.

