#### Exclusion criteria

A potential subject who meets any of the following criteria will be excluded:- Age under 18;- Not able to provide informed consent;- Previous surgical cubital tunnel release or other surgery performed in the same elbow;- Subluxation palpable during elbow flexion pre-operatively or occurring during surgery after release for which a transposition of the ulnar nerve is needed.

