### Intervention

Patients will be randomized for the open cubital tunnel release or endoscopic cubital tunnel release. Both interventions are standard of care in the Jeroen Bosch Hospital. Patients who undergo a cubital tunnel release receive plexus or general anesthesia depending on the preference of the patient. After applying a pneumatic tourniquet, a longitudinal incision is made between the medial humeral epicondyle and the olecranon. The ulnar nerve is identified and released proximally and distally. The nerve branches of the flexor carpi ulnaris are identified. After wound closure with a resolvable suture, the patient receives a pressure bandage in a 45 degrees flexion and the bloodless field is abolished. Both the open and endoscopic release are performed in the same manner, except the length of the incision which is smaller in the endoscopic release; after identification of the ulnar nerve, the endoscope is inserted and the nerve is released with use of the endoscope. The HOPKINS ® Telescope 30° (4 mm, 18 cm) by Karl Storz. In addition, patients can watch the nerve release during the operation or after the surgery.

Both patient groups receive the same aftercare. After two days, the pressure bandage can be taken off and full active mobilization of the elbow is allowed. After two weeks full use of the arm (work, sport and axial load) is allowed. Patients can take acetaminophen postoperatively. We do not recommend physiotherapy.

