#### Blinding

Patients, doctors and researchers will not be blinded for the treatment allocation. The nature of our study does not allow for blinding of the aforementioned parties. Unblinding does therefore not apply.

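### The trial is declared non-inferiority but every analysis is fixed as intention-to-treat, so any switching between techniques can favour a non-inferiority conclusion

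*Protocol article*

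**What the plan says.** The design is declared twice. The abstract's Methods paragraph says "A prospective single-center open randomized non-inferiority trial will take place", and Trial design says "This is a prospective randomized non-inferiority trial with two parallel study groups". The Objectives section points the other way: "We hypothesize that endoscopic cubital tunnel release is more effective in treating cubital tunnel syndrome than open cubital tunnel release".

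On the analysis population, the Analysis plan says "All analysis will be on an intention- to-treat basis". The article names no per-protocol or as-treated set. Its only decision criterion is a p-value below 0.05 with Bonferroni correction. It states no non-inferiority margin and no rule that compares a confidence bound with one.

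Three other statements bear on the point. Under Intervention: "Both interventions are standard of care in the Jeroen Bosch Hospital" and "Both the open and endoscopic release are performed in the same manner, except the length of the incision which is smaller in the endoscopic release". Under Blinding: "Patients, doctors and researchers will not be blinded for the treatment allocation". One exclusion criterion can take effect only in the operating room: "Subluxation palpable during elbow flexion pre-operatively or occurring during surgery after release for which a transposition of the ulnar nerve is needed".

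**The concern.** For a superiority question, ITT is the natural primary set. Patients who receive the other technique shrink the observed difference, which makes a superiority claim harder. For a non-inferiority question the same shrinkage makes the claim easier, because a difference near zero is what supports it. With ITT as the only permitted set, a finding of no worse could reflect the technique or could reflect switching, and the report would have no planned analysis to tell the two apart.

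The ITT statement also sits badly with the exclusion of patients whose nerve subluxates during surgery and needs transposition. That exclusion can fall after randomisation. If such patients are removed, the analysed set is not a full ITT set.

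**Working it through.** **The plan's own figure.** Sample size, recruitment and consent gives 144 patients, raised to 160 for 10% dropout. 144 / 0.9 = 160, which reproduces. At 1:1 allocation, 144 is 72 per arm. The 144 itself does not follow from the stated inputs alone, because the longitudinal formula also needs a within-patient correlation and a number of measurements, and neither is given. It is used below only as the planned number of evaluable patients.

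**Inputs from the document.** SD 0.7 and 72 per arm. The BCTQ minimal clinically important changes are 0.4, 0.7 and 0.7 (symptoms) and 0.3, 0.3 and 0.4 (function).

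**Assumptions, because the document gives no figure.**
- Margin M of 0.3, 0.4 or 0.7. These are the three distinct values above; the article does not call any of them a margin.
- Net share c of patients who receive the other technique and take on its mean result: 2% to 15%.
- One-sided level 2.5%, a single time point, no Bonferroni correction.
- True difference equal to M, so that any non-inferiority claim is false.

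**Formulas.**
- SE = 0.7 × √(2/72) = 0.1167
- Expected ITT difference = M × (1 − c)
- False non-inferiority rate = Φ(−1.96 + c × M / SE)

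**Worked cases at c = 10%.**
- M = 0.3: ITT difference 0.27; Φ(−1.96 + 0.03/0.1167) = Φ(−1.703) = 4.43%
- M = 0.4: ITT difference 0.36; Φ(−1.96 + 0.04/0.1167) = Φ(−1.617) = 5.29%
- M = 0.7: ITT difference 0.63; Φ(−1.96 + 0.07/0.1167) = Φ(−1.360) = 8.69%

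**Full range (nominal rate 2.5%).**

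| Net switching | M = 0.3 | M = 0.4 | M = 0.7 |
|---|---|---|---|
| 2% | 2.82% | 2.93% | 3.29% |
| 5% | 3.35% | 3.68% | 4.85% |
| 10% | 4.43% | 5.29% | 8.69% |
| 15% | 5.77% | 7.41% | 14.46% |

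**Revision surgery is a different mechanism.** Assume 10% of one arm and 5% of the other are revised, a failed release scores 1.0 point worse, and the techniques do not otherwise differ. Without any benefit from revision, the ITT difference is 0.10 × 1.0 − 0.05 × 1.0 = 0.05. If revision recovers half the loss it is 0.025, and if it recovers all of it, 0. A per-protocol set that drops revised patients shows 0 in all three cases. ITT can therefore retain a signal of failure that a carelessly built per-protocol set removes.

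**The case against.** The strongest reply is that the article describes no switching at all. It mentions no conversion, refusal of the allocated technique or revision, and gives no rates. A reader might infer that switching is easy here, because the two procedures are similar, both are standard care and nobody is blinded. Those statements make switching possible. They do not say that an endoscopic incision may be extended to an open release or that a randomised patient may have the other technique, and the allocation section says that assignment follows the randomisation module. This part of the objection stands, so the size of the effect is an assumption throughout.

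A reader might also infer that every conversion, refusal and revision pulls the arms together. That is not supported either. A conversion that ends badly counts against its own arm under ITT, and the revision example shows that the direction depends on how well revision works.

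Next, the Objectives state superiority, for which ITT is the right primary set. That is correct, and it makes this point conditional on the declared design. It does not remove the point while two places in the article still say non-inferiority. The missing margin is a separate defect and does not cure this one.

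A per-protocol set also has its own bias. Removing conversions or failures can flatter the technique in which they occur and so favour non-inferiority. This stands and shapes the fix.

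Last, supportive analysis sets are commonly left to a statistical analysis plan. Here the wording covers all analyses, so a later plan that added a per-protocol analysis would contradict the article rather than complete it.

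**Conclusion.** The point holds conditionally. If the trial remains non-inferiority, fixing ITT for all analyses is anti-conservative to the extent that patients receive the other technique. At 10% net switching, the nominal 2.5% error would become about 4.4%, 5.3% or 8.7% for margins of 0.3, 0.4 or 0.7.

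These figures rest on assumed margins, an assumed switching rate and a single-time-point standard error. The planned repeated-measures GEE and the Bonferroni correction would change them. The 8.7% uses the largest of the three candidate margins and should not be read as an expected value. If few or no patients switch, the effect is negligible: at 2% the rate is 2.8% to 3.3%.

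It would go too far to say that the plan will produce a false non-inferiority claim, or that revision surgery biases it in a known direction.

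Separately, and without any assumption about rates, the intra-operative exclusion criterion and the ITT statement conflict wherever that exclusion falls after randomisation.

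**What to change.** 1. Reconcile the declared design (abstract Methods, Trial design) with the hypothesis under Objectives. The remaining steps depend on the outcome.
2. If non-inferiority is kept, state the margin and change the Analysis plan so that the primary BCTQ GEE is run on the ITT set and also on a per-protocol set defined by the technique actually completed. Retain ITT, and claim non-inferiority only if the two analyses are consistent.
3. Do not drop revised patients from the per-protocol set. Report its results with and without post-revision scores, and report how many patients were left out because the technique completed was not the one allocated. Removing conversions or failures can itself favour non-inferiority.
4. If superiority is chosen, ITT stays primary and per-protocol becomes a sensitivity analysis.
5. In either case, record the technique completed and any revision of that elbow with its date.
6. In either case, reconcile the exclusion for subluxation found during surgery with the ITT statement, so that it is clear how patients already randomised are handled in the analysis.

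The cost is extra fits of a model already planned and a few data fields, with no additional patients or visits. The per-protocol comparison is not fully protected by randomisation, so it supports ITT and does not replace it. The non-inferiority claim also becomes slightly harder to make. With the single-time-point SE and a true difference of 0, leaving out 5% to 15% of patients gives per-protocol power of 0.71 to 0.66 at a margin of 0.3 (0.73 with all 144), or 0.92 to 0.89 at a margin of 0.4 (0.93 with all 144).

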### Outcomes

#### Primary outcome

The difference in change (Δ, preoperatively and postoperatively) in BCTQ score between both treatment groups at 3, 6 and 12 and 18 months follow-up.

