### Sample size, recruitment and consent

Malay et al. identified a minimal clinically import change (MCIC) at 3, 6, and 12 months’ time-points of 0.4, 0.7, and 0.7 points on a 5-point scale for symptom severity score of the BCTQ questionnaire and 0.3, 0.3, and 0.4 points on a 5-point scale for function status scale [19]. The standard deviation used is 0.7, based on a 12 months follow-up after decompression [20].

Using a sample size formula for continuous outcomes in a longitudinal study, a total of 144 patients will be needed (α = 0.05, β = 0.80). Taking into account a dropout of 10%, we will include 160 patients.

Patients will be identified and invited for the study at the neurological outpatient clinic. Study information will be given and time to overthink participation. During the first outpatient clinic visit at the plastic surgery department, patients will get the chance to ask questions and sign written informed consent with the surgeon or resident present.

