### Statistical methods

#### Primary study parameter

Difference in change in BCTQ: Linear generalized estimating equation (GEE) analyses will be used to study the longitudinal relationship between treatment group (determinant) on the one hand, and BCTQ score (outcome variable) on the other hand. This will be performed for the different domains of the BCTQ. This results in a single regression coefficient representing the population average difference in the outcome variable over time that incorporates between-subject and within-subject correlations.

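### Primary BCTQ result: no rule says which domain decides, and single-step Bonferroni gives up power that Holm keeps at the same family-wise error

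*Protocol article*

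**What the plan says.** All references are to the Protocol article.

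- **Primary outcome** gives one outcome, the between-group difference in change "in BCTQ score between both treatment groups at 3, 6 and 12 and 18 months follow-up".
- **Primary study parameter** fits a linear GEE and adds: "This will be performed for the different domains of the BCTQ". For each fit it states: "This results in a single regression coefficient representing the population average difference in the outcome variable over time".
- **Sample size, recruitment and consent** names two BCTQ scales with different minimal important changes at 3, 6 and 12 months. The first entry reads "0.4, 0.7, and 0.7 points on a 5-point scale for symptom severity score of the BCTQ questionnaire". For the other scale the values are lower: "0.3, 0.3, and 0.4 points on a 5-point scale for function status scale". It concludes that "a total of 144 patients will be needed (α = 0.05, β = 0.80") before dropout.
- **Analysis plan** sets the threshold, "Values of *p* < 0.05 will considered statistically significant", and the correction, "We will correct for multiple testing, *P*-values will be corrected by the Bonferroni method". It does not say which tests form the corrected family.
- **Trial design** calls the trial non-inferiority. **Objectives** states a superiority hypothesis for endoscopic release.

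**The concern.** One primary outcome is declared, but one coefficient per domain is estimated, and nothing links the coefficients to a single verdict. If symptom severity is significant and function status is not, or the reverse, the text does not say what the trial has shown. Treatment allocation is open, so the choice of which domain to stress should not be left until results are known.

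The correction method makes that outcome more frequent than it has to be. With two domains, single-step Bonferroni compares each P-value with 0.025, even after the other domain has been rejected. Suppose one domain has P below 0.025 and the other has P = 0.03. Bonferroni gives an adjusted P of 2 × 0.03 = 0.06, not significant. Holm rejects the first domain and then tests the second at 0.05, so it is significant at 0.03. The overall error guarantee is the same.

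**Working it through.** **Inputs from the document.** Alpha 0.05; power 0.80 (the article's β = 0.80, read as power); SD 0.7; 144 evaluable patients, so 72 per arm at 1:1; two named BCTQ scales.

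**Assumptions, not in the document.** Two-sided tests; a family of exactly two tests, one coefficient per domain; a correlation between the two test statistics of 0.5, with a range.

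**The plan's own figure.** 144/0.9 = 160 reproduces. The 144 itself cannot be pinned down, because the article does not say which difference, within-patient correlation (ρ) or number of measurements (T) was used. Per arm, n = 2 × SD² × (z_α + z_β)² × (1 + (T − 1)ρ)/(T × δ²).

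- δ = 0.3, two-sided 0.05, T = 3, ρ = 0.75: 2 × 0.49 × (1.960 + 0.842)²/0.09 = 85.5; × 2.5/3 = 71.2, rounded up to 72 per arm, total 144.
- δ = 0.3, two-sided 0.025, T = 4, ρ = 0.60: 2 × 0.49 × (2.241 + 0.842)²/0.09 = 103.5; × 2.8/4 = 72.4, rounded up to 73 per arm, total 146.

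So 144 does not show whether a Bonferroni split was built in.

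**Why the error rates match.** Both methods make a first rejection only if the smaller P is at most 0.05/2. The chance of any rejection is therefore identical, and so is the family-wise error when both nulls are true. Holm then tests the remaining P at 0.05 instead of 0.025, which can only add rejections.

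**Scenario A: 80% unadjusted power on each domain.** The mean of each z statistic is 1.960 + 0.842 = 2.80. Bonferroni power per domain is Φ(2.80 − 2.241) = Φ(0.56) = 71%. Joint results come from 300,000 simulated pairs per row.

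| Correlation | Both significant, Bonferroni / Holm | Split, Bonferroni / Holm | Family-wise error, both nulls true (either method) |
|---|---|---|---|
| 0.3 | 54.5% / 65.8% | 33.7% / 22.3% | 4.8% |
| 0.5 | 57.3% / 67.7% | 28.1% / 17.7% | 4.7% |
| 0.8 | 62.5% / 71.4% | 17.5% / 8.7% | 4.0% |

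Holm power per domain is 76 to 77%. At correlation 0.5 the chance of at least one rejection is 57.3 + 28.1 = 85.4% with Bonferroni and 67.7 + 17.7 = 85.4% with Holm.

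**Scenario B: the article's SD and sample size, one measurement per patient.** For a true difference of 0.3, z = 0.3/(0.7 × √(2/72)) = 2.57. Power is Φ(2.57 − 1.960) = 73% at 0.05 and Φ(2.57 − 2.241) = 63% at 0.025. Simulation of 1,000,000 pairs at correlation 0.5 gives:

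| True differences | Both significant, Bonferroni / Holm | Split, Bonferroni / Holm |
|---|---|---|
| 0.3 and 0.3 | 47.2% / 58.1% | 31.4% / 20.5% |
| 0.4 and 0.3 | 59.6% / 69.9% | 32.0% / 21.7% |
| 0.3 and 0 | 1.4% / 3.0% | 62.7% / 61.1% |

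Over correlations 0 to 0.9, with 0.3 on both domains, splits run from 46.6% down to 13.6% with Bonferroni and from 34.0% down to 5.2% with Holm, a cut of 8 to 13 points. In the last row the null domain is rejected in 2.5% of trials with Bonferroni and 4.0% with Holm. Holm spends more of the allowed error but stays under 5%.

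**If both domains must succeed.** No correction is needed for that claim. Testing each at 0.05 gives both significant in 59.4% of trials (0.3 and 0.3, correlation 0.5), against 58.1% with Holm and 47.2% with Bonferroni.

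**The case against.** The strongest reply is that Bonferroni is a valid and common choice, so the Analysis plan contains no error here. That stands: it controls the family-wise error, and the point is lost power only.

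Second, a reader might infer that the primary analysis has no deciding contrast at all. The document does not support that. Within each domain the Primary study parameter section names the time-averaged coefficient. What is open is which domain's coefficient counts.

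Third, a reader might infer that Holm cures the split-verdict problem. It does not. In Scenario A 9 to 22% of trials still split. When only one domain truly differs, about 61% split under Holm, and there a split is the correct answer. Only a stated decision rule gives a split a meaning.

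Fourth, it is tempting to say that Bonferroni buys nothing in exchange. That goes too far. The Analysis plan speaks of P-values only, but the Trial design section labels the trial non-inferiority. If that question is judged by confidence limits, Bonferroni has simple simultaneous intervals and Holm does not.

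Fifth, the test family and the claim rule may be set out in an analysis plan that is not shown. That is fair, and their absence from a condensed article is not in itself a fault. The article does fix the correction method, however, and it pairs a single primary outcome with several domain coefficients. If the corrected family also includes secondary tests, the two-test figures do not describe the rule as applied.

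**Conclusion.** The point holds as an efficiency improvement together with a clarification of the decision rule. It is not an error in type I error control. With two domains, 80% unadjusted two-sided power on each and correlation 0.5 (range 0.3 to 0.8), Holm raises the chance that both domains are significant from 57% to 68% and lowers split verdicts from 28% to 18%. About a third of the splits ((28.1 − 17.7)/28.1 = 37%) come from the single-step rule alone. The gain needs true effects on both domains; with an effect on only one it is 1 to 2 points. The chance of at least one significant domain does not change. The correlation, the two-test family, the two-sidedness and the equal power per domain are assumptions; the different minimal important changes for the two scales make equal power a simplification.

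**What to change.** 1. In Analysis plan, replace Bonferroni with the Holm step-down method for the P-values.
2. In Primary study parameter, name the symptom severity and function status coefficients as the primary family, tested by Holm at an overall two-sided 0.05.
3. State that a difference is claimed only for a domain whose Holm-adjusted P is below 0.05, and for the BCTQ as a whole only if both are. If a both-domains claim is the only one wanted, test each at 0.05 without correction and say so.
4. If the non-inferiority question is judged by confidence limits, keep Bonferroni-adjusted intervals for that judgement.

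The cost is a few sentences and one software option, with no extra patients or data. The downside is that Holm has no simple matching simultaneous intervals, which item 4 covers. The change should be made before outcome data are analysed by arm.
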